## Abstract

**Background:**

Severe mentally ill (SMI) patients have a reduced life expectancy of 13–30 years compared to the general population, largely due to an increased risk of cardiovascular mortality. Unhealthy lifestyle behaviours in SMI patients contribute to this increased risk. The obesogenic living environment of patients in residential facilities may even pose an extra risk. Although several studies have shown positive effects of lifestyle interventions on SMI patients’ weight status, studies including residential patients and their obesogenic environment are scarce. This paper describes the Effectiveness of Lifestyle Interventions in PSychiatry trial (ELIPS). The goal of this trial is to improve cardiometabolic health in severe mentally ill residential patients by addressing the obesogenic environment.

**Methods/design:**

The ELIPS study is a multi-site cluster randomised controlled trial (RCT) based on the principles of a pragmatic RCT. All residential and long-term clinical care teams of two large mental health care organisations in the North of the Netherlands serving SMI patients are invited to participate. The intervention is aimed at team level. Lifestyle coaches first develop a team specific lifestyle plan that tailors the ELIPS goals and protocol and then train teams on how to create a healthy environment and stimulate healthy behaviours in patients. After three months, teams take over the intervention after they have set out goals to achieve in the following nine months. In this phase, adherence to the lifestyle plan and pre-set goals is monitored. Patients in the control arm receive care as usual. Primary outcome measure is waist circumference at three and 12 months after baseline.

**Discussion:**

ELIPS is different from previously published lifestyle intervention studies in three ways. First, it follows the principles of a pragmatic design, which enables the examination of effects in everyday practice. Second, by implementing the intervention at team level, we expect lifestyle activities to be maintained when interventionists leave. Last, by targeting the obesogenic environment we create a prerequisite for any sustainable health improvement, as patients can only make healthy choices in a healthy living environment.

**Trial registration:**

Nederlands Trialregister NTR2720 (Dutch Trial Register, www.trialregister.nl). Registered 27 January 2011.

## Background

The life expectancy of patients with severe mental illness (SMI) is 13–30 years less than that of the general population [1]. This is largely due to an increased risk of cardiometabolic disease, including type 2 diabetes and cardiovascular disease. High rates of smoking, poor dietary habits, a sedentary lifestyle and side effects of type of antipsychotic medication are all modifiable risk factors that contribute to the increased mortality [2,3]. Numerous studies have investigated the effectiveness of lifestyle interventions in SMI patients [4-8]. These included single group interventions, non-randomized controlled trials and randomized controlled trials (RCTs). Although most studies are small and vary in their methodological quality, they all show that lifestyle interventions are feasible in SMI patients and can lead to weight loss and improvements in cardiometabolic health [9]. Mean weight losses across studies by treatment duration were 2.63 kg for 12- to 16-week interventions, 4.24 kg for 6-month interventions and 3.05 kg for 12- to 18-month interventions according to Gabriele et. al. [10].

In the current literature, lifestyle intervention studies in SMI residential patients are scarce. In their systematic review on exercise interventions for mentally ill inpatients, Stanton and Happell [11] found eight small studies with sample sizes varying from 12 to 39 patients. The somatic health of SMI patients living in residential facilities is not better than in SMI outpatients [11,12]. Moreover, residential patients’ living environment may pose an extra risk, as a lack of daily activities and an abundant provision of unhealthy food products may lead to an obesogenic environment. Swinburn et. al. [13] conceptualized the role of the obesogenic living environment as “the sum of influences that the surroundings, opportunities, or conditions of life have on promoting obesity in individuals or populations” (p. 564). Residential facilities seldom offer vocational rehabilitation activities, sports or physical activities, and residential patients are usually not involved in housekeeping chores. Patients may be offered meals from a central kitchen that are not always based on healthy nutrition guidelines, and snacks and other unhealthy food products are often readily available. It seems inefficient, and even unethical, to motivate patients to adopt a healthy lifestyle in an environment that stimulates unhealthy behaviour. While the obesogenic elements in residential patients’ living environment may play an important role in the development of weight gain, they yield possibilities for prevention and weight reduction as well. As far as we know, only one small intervention study (N = 37 at 12-month measure) aimed to tackle the obesogenic environment of patients [14].

Besides the focus on the obesogenic environment and the residential SMI population, our trial has another feature distinguishing it from other studies in SMI patients, and that is the so called ‘small change approach’. Large initial weight loss has been associated with greater weight gain later on [15]. Furthermore, even when weight loss is low (≤3%), lifestyle changes such as aerobic exercise can have beneficial effects on cardiometabolic risk factors such as insulin resistance, elevated blood lipids, blood pressure and glucose metabolism [16]. And last, smaller lifestyle changes are more likely to be sustainable, leading to increased health gain in the long run. In a small RCT, Sbrocco et. al. (1999) compared a small change approach in eating behaviour to a traditional behavioural weight loss program [17]. Initially, participants of the traditional program lost more weight than the small change group, but after nine months, the small change group continued to lose weight while the traditional behavioural therapy group started to regain weight. These results have been replicated recently in a US veterans study where small changes in both nutrition and physical activity led to weight loss and maintenance [18]. As far as we know, this small change approach has not been carried out in studies involving SMI patients, while they would particularly benefit from this approach considering the cognitive deficits and negative symptoms that are characteristic of this patient group.

Until now, most high quality lifestyle intervention studies in SMI patients have been RCTs. While a traditional measurement-blinded RCT is the preferred design to evaluate the efficacy of a lifestyle intervention, it also has important disadvantages. Often the most motivated patients are (unintentionally) selected for a trial in a laboratory setting. It has been shown that these patients are usually not comparable to patients in real-life settings [19]. Additionally, in a traditional RCT, lifestyle interventions are often strictly organised and supervised by interventionists, whereas in daily practice “health care interventions are seldom given under such circumstances”. (p. 2) [20]. The lack of external validity poses a threat to the effectiveness of interventions in daily practice, with not-so-motivated patients and without the dedicated attention of interventionists. For this reason, we designed a RCT with a pragmatic character to evaluate the effectiveness of a lifestyle intervention in a real-life setting with local staff members [20].

The aim of the current paper is to give a detailed portrayal of a clustered randomised controlled trial evaluating the effectiveness of a lifestyle intervention, the Effectiveness of Lifestyle Interventions in PSychiatry trial (ELIPS). This combined diet and physical activity lifestyle intervention is designed to improve the obesogenic environment of SMI residential patients. It is hypothesised that changing the obesogenic environment by engaging patients in physical activities and offering them the choice for healthy products, will improve cardiometabolic health in this patient group.

## Methods

ELIPS is a multi-site trial designed according to the principles of a pragmatic RCT to allow evaluation of the intervention in real-life care facilities. Details are described below according to the CONSORT statement for cluster randomised trials [21] and the extension of the CONSORT statement for pragmatic trials [22]. The Medical Ethical Committee for Research in Mental Health Care (Metigg) approved the study protocol. The trial is registered in the Dutch Trial Registry (Nederlands Trialregister NTR2720, www.trialregister.nl. Registered 27 January 2011).

### Participants

All residential and long-term clinical care teams of two large mental health organisations in the North of the Netherlands, a catchment area of 1.2 million inhabitants, are invited to participate in the study (N = 30). One residential team exclusively serving patients suffering from Korsakov’s syndrome is excluded. Team leaders are informed by an invitation letter followed by a meeting to explain the study. Teams are visited by the project leader to explain the aims of the study and answer questions. Teams serve severe mentally ill patients, often with a diagnosis of schizophrenia or other psychotic disorder, most of whom have been living in residential facilities for at least 10 years. Caseload sizes vary from 20 to 65 patients per team. In the Netherlands, patients living in residential facilities live as independently as possible, with a team of professionals nearby. Patients are housed alone or in small groups in a community neighbourhood. Long-term clinical care facilities provide more intensive professional care and assistance in activities of daily living. Housing is provided in the sheltered and safe environment of the mental health care organisation.

All patients are invited to participate, as they are all at increased risk of unhealthy lifestyle habits due to their obesogenic living environment, and all patients are considered to have an increased cardiometabolic risk. Exclusion criteria are age below 18, pregnancy and being unable to perform physical activity tests (e.g. wheelchair user). Patients not taking part in the yearly routine outcome monitoring (ROM, see ‘outcomes’), that is used for this study to monitor intervention effects, will not be included in the analysis. In the mental health organisation Lentis (~50% recruitment area) only patients using antipsychotic medication are routinely monitored. Therefore, patients from Lentis not using antipsychotic medication are excluded.

### Intervention

The ELIPS intervention is aimed at team level and focuses on achieving established ELIPS lifestyle goals. These goals are: 1. At least two physical activities per week, of which at least one moderately intensive; 2. At least three changes in daily food supply that favour health; 3. A weekly food workshop, in which patients learn to buy, cook and eat healthy food products; 4. A sustainable change in the obesogenic environment on organisation level. The ELIPS goals and subgoals are presented in Table 1. The intervention is implemented by lifestyle coaches; each team has two lifestyle coaches at its disposal. Before the start, lifestyle coaches receive two days of intensive training which consists of lectures and interactive sessions on SMI and its symptoms (positive and negative psychotic symptoms, depression), metabolism, healthy food products, physical activities suitable for SMI patients, motivational interviewing, the development over time of the obesogenic environment and ways to tackle it.

**Table 1 Tab1:** **Lifestyle goals of ELIPS intervention and examples from practice**

**Goal**	**Subgoal and example**
**1. Minimally two physical activities per week, one of them being intensive**	
	1.1 increase in daily physical activity on individual level
	*E.g. counselling conversations during a walk outside rather than sitting in the office; patients walk/cycle to shop for own groceries; patients walk/cycle to work rather than taking the bus.*
	1.2 increase in daily physical activity on group level (low intensity)
	*E.g. organise group walks one or twice a week.*
	1.3 participation in more intensive physical group activity (organised, medium intensity)
	*E.g. organise a weekly football activity, organise a WII-sports activity, visit a fitness centre once a week, go for a swim once per two weeks.*
**2. Minimally three improvements in food supply**	
	2.1 decrease in intake of saturated fat and trans fatty acids
	*E.g. replace high-fat cheese by low-fat cheese; limit consumption of sweetened dairy products; limit cake consumption (luxury cookies only on Sundays).*
	2.2 increase in intake of fibres
	*E.g. replace white bread by whole wheat bread; replace white rice/pasta by whole rice/pasta; serve fruit and vegetables during activities.*
	2.3 decrease in energy intake
	*E.g. replace products by light versions; replace butter by (diet) margarine; replace almond paste cake by gingerbread.*
	2.4 decrease in intake of salt
	*E.g. buy fresh vegetables instead of canned vegetables; replace crisps by vegetables (cucumber); offer snacks in small portions, and/or only in the weekends.*
**3. Minimal one food focused activity per week**	
	*E.g. create a daily fruit moment; make a shopping list together; buy healthy groceries together; cook a healthy meal together; play a food quiz; make smoothies; learn to decipher the list of ingredients.*
**4. Adjustment of the obesogenic environment on organisational level**	
	*E.g. limit access to food cupboards, adjust food supply in canteen (selling fried snacks only twice per week); provide a gym; set up contracts with fitness centres; purchase a WII sports; prepare breakfast every morning; put nutrition and physical activity standard on the team meeting’s agenda.*

The trial consists of a preparation phase, an implementation phase and a monitoring phase. An overview of phase-specific tasks is given below. The team specific interventions are outlined in the one-month preparation phase. During this period, lifestyle coaches become acquainted with team members, patients and the location. The coaches screen which healthy and unhealthy behaviours and lifestyle activities take place and seek possibilities for improvement that comply to the ELIPS goals. To increase activity participation and sustainability, lifestyle coaches make a list of activities that patients and team members find appealing. Structured protocols describe planning of lifestyle activities (i.e. minimal two physical activities and one food workshop per week) and form the basis of each intervention to insure that team specific interventions are compatible and all teams pursue the ELIPS lifestyle goals. The team specific lifestyle plan includes a detailed program of exercise and food activities according to the ELIPS goals and is adjusted to the team’s opportunities, patients’ preferences and the logistic possibilities of the location. This tailor-made lifestyle plan colours this pragmatic cluster randomised trial.

Description of tasks and schedule of ELIPS intervention:*-1 - 0 months Preparation phase*Lifestyle coaches visit intervention teams to become acquainted with the team, patients and location.Lifestyle coaches explore which (un)healthy behaviours and activities take place.Lifestyle coaches inquire which lifestyle activities patients and teams prefer and examine logistic possibilities for these activities.Lifestyle coaches create a team-specific lifestyle plan based on ELIPS lifestyle goals, structured protocols and the preferences and possibilities of the team and patients.Baseline measures: ROM-nurses carry out ROM measurements, research assistants carry out additional measures. See Table 2 for an overview of measurements.*0 - 3 months Implementation phase*Lifestyle coaches organise lifestyle activities and workshops. The team is involved in the organisation and motivates patients to participate. Lifestyle coaches first demonstrate the activities, then co-organise them out together with the team, while towards the end, they supervise team members who, over time, are made responsible for carrying out the lifestyle activities themselves.Lifestyle coaches transfer their knowledge and skills of healthy behaviours to the team.Lifestyle coaches assist the team in setting concrete goals in order to improve or maintain a healthier lifestyle after the lifestyle coaches have gone.Structural changes to adjust the obesogenic environment are explored and implemented.*3 - 12 months Monitoring phase*3-months measures: ROM-nurses carry out ROM measurements, research assistants carry out additional measures. See Table 2 for an overview of measurements.Team continues lifestyle activities, aiming to achieve the pre-defined goals.Start monthly monitoring visits. A lifestyle coach evaluates with the team the pre-defined goals, detects obstacles in achieving these goals, solves observed obstacles. If necessary, recommendations for improvements are made.12-months measures: ROM-nurses carry out ROM measurements, research assistants carry out additional measures. See Table 2 for an overview of measurements.12-months monitoring visit: final monitoring wherein goals are evaluated and recommendations are made to sustain the lifestyle activities.

In the three months intervention phase the team specific intervention is implemented. Lifestyle coaches first demonstrate the activities, then carry out the activities together with team members and finally supervise while team members carry out the activities themselves. During the entire implementation phase, lifestyle coaches train teams how to create a healthy environment for their patients and stimulate a healthier lifestyle in their patients. Lifestyle coaches transfer their knowledge and skills to the team members by demonstrating exercise and food activities as well as using motivation and counselling techniques to stimulate patients to adopt a healthier lifestyle. Exercise activities are for instance walking, low-intensity sports such as jeu de boules, badminton, table tennis, bicycling. The intensity and frequency of the exercises will gradually increase. Food workshops could be for example cooking a vegetable soup together with patients, making smoothies, teaching how to read a list of ingredients, demonstrating the amount of sugar in soft drinks and juices and doing affordable fruit and vegetable shopping in the market place together. Examples of adjusting the environment are restricting access to food cupboards, setting up contracts with local gyms, placing fruit on the table. More practical examples are presented in italics in Table 1. At the end of the three months implementation period, the team sets goals to achieve in the following 9 months. During this 9 month monitoring phase a lifestyle coach visits all intervention teams monthly and will discuss with the team and team leader whether goals are achieved, if there are any barriers in achieving the goals and look for ways to remove the obstacles.

The intervention has two distinct features that are not described in lifestyle interventions presented in the literature [9]. First, the intervention is implemented at team level. We hypothesise that team members will be able to induce the largest change in their patients’ lifestyle behaviours as they already have a relationship with patients. Moreover, it will be easier to continue healthy lifestyle activities after the intervention period, when these activities are imbedded in the team and in the team’s schedule. Also, team members might become stimulated to adjust their own lifestyle as well and in doing so, set a good example. The second distinct feature of the intervention is the focus on changing the obesogenic environment. Stimulating patients to engage in healthy lifestyle behaviour can only be a success when the environment offers sufficient possibilities for healthy lifestyle choices. Sport facilities and exercise activities must be available, as well as healthy food products. Likewise, the environment can discourage unhealthy behaviours, for instance by narrowing the opening hours of canteens serving fried snacks. It is hypothesised that an intervention with these distinct features will lead to changes in lifestyle behaviour in patients that are highly sustainable.

### Control group

The patients in the control arm receive care as usual. No ELIPS lifestyle intervention activities will be carried out in the control teams. Teams or individual team members are not prohibited to discuss healthy lifestyle behaviours with their patients or organise healthy lifestyle activities. All healthy lifestyle activities will be documented and new initiatives are reported to the researchers. When ethically and logistically possible, researchers will ask teams to delay implementation of these activities until the end of the study. Monitoring visits by lifestyle coaches will establish possible changes in intensity or frequency of existing lifestyle activities during the study.

### Objectives

The primary objective is to determine the effect of the ELIPS intervention on body fatness defined by waist circumference at 3 and 12 months. We hypothesise that the ELIPS intervention group will have a reduced or stabilized waist circumference whereas the waist circumference of the control group will increase. The secondary objective is to determine the effect of the ELIPS intervention on other cardiometabolic risk factors, i.e. blood pressure, lipids and glucose metabolism. Furthermore, the aim is to determine the effect of the ELIPS intervention on lifestyle behaviours (physical fitness, physical activity, dietary habits), mental health (positive and negative psychotic symptoms, depressive symptoms), quality of life and psycho-social functioning of patients. For all these objectives, the difference in effect across age groups and gender will be studied. In view of the pragmatic trial, a process evaluation on the degree and quality of the implementation of the intervention and changes at team and organisation level is foreseen. The outcomes of this evaluation will be used to investigate differences in effectiveness between teams. Lastly, the effect of the ELIPS intervention is investigated in terms of cost-effectiveness. The cost-effectiveness of lifestyle interventions has not been researched in severe mentally ill residential patients and this study will give an indication of the costs related to health improvements in this population.

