### Sample size

The primary objective in this study is to detect a difference in waist circumference with clinical significance. Sample size calculations show that to detect a significant change of −5% waist circumference [39] (alpha =0.05, power 0.90), 219 patients are needed in both intervention and control arm. Research in psychiatric patients usually shows a high drop-out rate. However, since in this project patients are living intramurally and most measurements are part of standard care, it is expected that the drop-out rate, once having signed an informed consent, will not exceed 10%. Therefore the target number of patients to include in both intervention and control arm is 240 (N = 219 + 10% drop-out). In both mental health organisations together, approximately 1000 eligible SMI patients live in residential or long-term clinical care facilities. Results from a pilot study show that two thirds of patients will successfully participate in the measurements which means that the two organisations will suffice to include the necessary 240 patients per arm. This number will also be sufficient to demonstrate for example a 4.7% reduction in plasma glucose. The clustered nature of the trial requires some extra thoughts on loss of power in multilevel analyses. However, as we a have a large number of clusters (13 clusters; see below) and a large number of patients per cluster (range from 44 to 130), the interdependency of observations will be limited. This may justify using individual patient rather than clustered sample size calculations [40].

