### Statistical methods

Data will be analysed with intent-to-treat analysis because all patients within intervention teams are expected to be exposed in some extent to the adjusted obesogenic environment. A multi-level linear mixed model will be used in order to evaluate the effect of intervention group on waist circumference at 3 and 12 months after baseline, with intervention group (i.e. belonging to an intervention or control team) being the main independent variable. The model accounts for the clustering of teams and the longitudinal character of the trial. Adjustments for baseline scores will be made and interactions with age and gender will be studied. Secondary outcomes, other cardiometabolic risk factors, lifestyle behaviours, mental health, quality of life and psycho-social functioning, will be analysed in the same way as waist circumference.

The number of achieved ELIPS goals, the degree of additional changes in the environment, the stability of teams, and knowledge, attitudes and self-efficacy of teams and team leaders towards a healthy lifestyle will be scored to give insight in the variation and quality of implementation of the intervention per team. Subgroup analyses will be done to find out if there are differences in outcomes between patients within teams with more of less successful implementation of the intervention. This might also give an idea of minimal conditions needed for this intervention to be implemented to a certain degree.

An economic evaluation will be conducted to assess the cost-effectiveness of the lifestyle intervention compared to care as usual in severe mentally ill residential patients. The analysis will be performed from a societal perspective; costs in and outside the healthcare sector will be included. Results will be expressed in terms of incremental costs per percentage change in waist circumference. Furthermore, a cost-utility analysis will be conducted with the QALY (Quality Adjusted Life Years) as primary outcome measure. Finally, potential long-term economic consequences due to reduced incidence of diabetes and other cardiovascular diseases will be explored.

Missing data and drop-outs will be analysed and accounted for by multiple imputation if the assumption of data missing at random (MAR) is not violated.

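### Waist circumference at 3 and at 12 months is primary with equal status, but one alpha of 0.05 and one 5% effect are tied to neither time, and no rule says what counts as success

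*Protocol article*

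**What the plan says.** Four places in the protocol article bear on this.

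- **Abstract, Methods/design:** "Primary outcome measure is waist circumference at three and 12 months after baseline".
- **Objectives:** the primary objective is the "effect of the ELIPS intervention on body fatness defined by waist circumference at 3 and 12 months". The hypothesis that follows (waist reduced or stable under the intervention, rising in controls) carries no time point.
- **Sample size:** the calculation is made "to detect a significant change of −5% waist circumference", with "alpha =0.05, power 0.90), 219 patients are needed in both intervention and control arm". One alpha and one effect are given. Neither is assigned to 3 or 12 months, and alpha is not divided between them.
- **Statistical methods:** a multilevel linear mixed model evaluates the "effect of intervention group on waist circumference at 3 and 12 months after baseline, with intervention group" as the main independent variable. No contrast, joint test, test order or rule for combining the two times is stated. Secondary outcomes follow the same approach.

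The Intervention section shows what the times represent. Month 3 closes the phase led by the lifestyle coaches. Month 12 closes nine months in which the teams run the activities, with monthly monitoring visits.

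**The concern.** Which time point carries the primary test is a protocol-level choice, because the sample size depends on it. The article does not leave that choice open for a later document. It gives two times equal primary status and then sizes the trial for one comparison. Several success rules fit the text, and they differ in error rate, in power and in the question they answer.

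The two times are not interchangeable. The abstract's discussion, the Intervention section and the Discussion all expect the benefit to last once the coaches leave. The Discussion also cites a three-month behavioural intervention whose effect had faded three months after it stopped. The Background describes small-change programmes as losing less weight at first but continuing to lose later. The article's own rationale therefore allows the effect to differ between 3 and 12 months. If the rule is chosen after the results are known, the primary conclusion could depend on that choice.

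**Working it through.** **Inputs.** From Sample size: alpha 0.05, power 0.90, 219 per arm, a 5% difference, individual-level calculation with no allowance for clustering. Not given, so assumed: two-sided testing; equal arms; a correlation between the 3- and 12-month test statistics of 0.5 to 0.9, with 0 as the limiting case.

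**1. The plan's own figure.** No SD is stated, so 219 cannot be reproduced independently. It can be solved backwards. From n = 2(1.960 + 1.282)² × SD² / 5², SD = 5 × √(219/2) / 3.2415 = 16.1% of mean waist. By construction, 219 per arm at this SD gives power 0.90 for one test at one time.

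**2. Success at either time or at both times, each tested at two-sided 0.05.** With (Z1, Z2) bivariate normal under no effect:

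- either time: error = 1 − P(|Z1| < 1.96, |Z2| < 1.96)
- both times: error = 0.05 + 0.05 − the value above
- both times: power = P(Z1 < 1.282, Z2 < 1.282), assuming a true 5% effect at each time

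| Correlation | Either: error | Both: error | Both: power |
|---|---|---|---|
| 0 | 0.0975 | 0.0025 | 0.810 |
| 0.5 | 0.0907 | 0.0093 | 0.832 |
| 0.7 | 0.0835 | 0.0165 | 0.847 |
| 0.8 | 0.0781 | 0.0219 | 0.856 |
| 0.9 | 0.0704 | 0.0296 | 0.869 |

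The either-time rule exceeds 0.05 throughout. The both-times rule does not, but its power is below the stated 0.90.

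**3. One averaged group effect.** This is a single test, so its error stays at 0.05. Suppose the true effect is 5% at 3 months and zero at 12 months, with equal variances and correlation r. The noncentrality is (3.24/2) / √((1 + r)/2).

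- r = 0.5: 1.62 / 0.866 = 1.87, so the test is significant about 46% of the time.
- r = 0.9: 1.62 / 0.975 = 1.66, so the test is significant about 38% of the time.

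These would be positive results with nothing maintained at 12 months.

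**4. Alpha split, 0.025 per time.** n = 2(2.241 + 1.282)² × (16.14/5)² = 259 per arm instead of 219. Keeping 219 gives power Φ(3.2415 − 2.2414) = 0.841 per time.

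**5. Fixed sequence, 12 months and then 3 months.** With no effect at either time, a false claim requires the 12-month test to reject, so the error is 0.05. The 12-month test keeps the full alpha, and 219 per arm still corresponds to power 0.90.

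**The case against.** The strongest reply is that the article never says success at either time is enough. It links the two times with the word for both, and it gives no success criterion. A reader might infer that a 3-month effect alone counts as a positive trial and that the error rate therefore exceeds 5%. The text does not support that as a statement of fact. A both-times rule, a joint test or an averaged test would all hold the error at or below 5%.

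A reader might also infer that the model permits only two separate tests or one average. That does not follow either. Calling intervention group the main independent variable identifies the exposure and does not rule out a group-by-time term. A model described as longitudinal fits several contrasts.

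Finally, this is a condensed article. Test order and multiplicity adjustment are commonly left to an analysis plan, and one may exist.

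Most of this stands, and it limits the point. The inflation is conditional, and the lack of model detail is not in itself a fault. What remains is in the article's own text: two co-equal primary times, and one alpha and one effect size attached to neither. It is also fair to say that making 12 months primary is a choice. The objective gives both times equal standing, and other error-controlling rules are legitimate.

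**Conclusion.** The point holds in a conditional form and is of moderate weight. The article gives 3 and 12 months equal primary status, sizes the trial for one unassigned comparison and leaves the success rule undetermined. If either time could count, the false-positive rate is about 7.0% to 9.1%, with a ceiling of 9.75%, and a transient effect could be reported as a positive primary result. If both times are required, error is held but power falls to about 83% to 87%. If the effect is averaged, error is held but the coach-led and team-led phases are blended.

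These figures rest on two-sided testing, an assumed correlation of 0.5 to 0.9 and, for power, an SD solved back from 219 with no clustering. The text neither adopts nor excludes the either-time rule, so the inflation is a risk that the wording leaves open and not an established property of the plan.

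**What to change.** Before outcome data are seen:

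- In Statistical methods, include a group-by-time term and name the group difference in waist circumference at 12 months as the primary contrast, at two-sided 0.05. Test the 3-month difference only if the 12-month difference is significant.
- In Objectives and the abstract, state that order. Twelve months is the natural first test because it matches the stated aim of maintenance after the coaches leave.
- In Sample size, attach the 5% effect to 12 months.
- State whether the secondary outcomes, and the cost per percentage change in waist circumference, refer to the same time.

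The cost is a few sentences, with no extra patients on account of multiplicity. The one real loss is that a 3-month effect cannot be claimed as confirmatory if the 12-month test fails. If the sponsor wants both times to keep equal standing, a joint test, a both-times rule or an alpha split would also control the error. In that case the chosen rule should be written down and its effect on power or sample size accepted openly.
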